## Eligibility Criteria

### Inclusion criteria

- Written informed consent must be obtained before commencing with any study assessment
- Healthy eyes with no anterior eye disease (i.e. lens opacities < grade 2 based on LOCS III) and no signs of retinal or optic nerve disease (diabetic retinopathy, glaucoma or age-related macular degeneration) based on ophthalmic examination (determined by an ophthalmologist, [name])
- Being able to follow the study protocol and able to walk unaided

### Exclusion criteria

- Inability to comply with study follow-up
- Participants having travelled across 2 or more time zones within 90 days before start of the study
- Addenbrooke's Cognitive Examination Score <82
- Deep brain stimulation, other device assisted therapies (i.e. red light therapy) or CNS surgery
- Any type of systemic disease or any medical condition (controlled or uncontrolled) other than PD that could be expected to significantly affect the health of a participant
- A periodic limb movement disorder index (Total PLMS arousal index) >15 events/hour in PSG
- Significant sleep apnea (that is not positional) and loss of REM atonia in PSG
- Recent or recurrent history of musculoskeletal injury or surgery
- Melatonin intake in the last two weeks

## Endpoints

### Primary

- Change from baseline to week 4 and week 6 in mean objective sleep macrostructure (polysomnography, PSG): Sleep stages (N1, N2, N3, REM), Total sleep time, Sleep onset latency, Stage REM latency, Sleep efficiency, Time awake, Total PLMS Arousal Index
- Change from baseline to week 4 and week 6 in mean DLMO decimal time

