### 2.2. Outcome measures

- Primary outcome measures:
  - Change in salivary Dim light Melatonin Onset (DLMO) before and after light intervention at week 4 and week 6.
  - Change in polysomnography parameters (i.e. total sleep time, sleep efficiency and latency and REM latency and time in sleep stages) before and after light intervention at week 4 and week 6.
- Secondary outcome measures:
  - Change in subjective sleep questionnaire results such as in Pittsburgh Sleep Questionnaire Inventory PSQI, Epworth Sleepiness Scale (ESS), Parkinson's Disease Sleepiness Scale before and after light intervention at week 4 and week 6.
  - Other secondary outcome measures are motor function (gait, balance and tremor) and melanopsin-mediated pupil function before and after light intervention at week 4 and week 6.
- Exploratory analysis will examine the effect of light on mood (Beck's Depression Inventory-II and quality of life (PDQ-39) before and after light intervention at week 4 and week 6.

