#### *Exclusion criteria*

- Inability to comply with study follow-up
- Participants having travelled across 2 or more time zones within 90 days before start of the study
- Addenbrooke's Cognitive Examination <82
- Deep brain stimulation, other device assisted therapies (i.e. red light therapy) or CNS surgery
- Any type of systemic disease or any medical condition (controlled or uncontrolled) other than PD that could be expected to significantly affect the health of a participant
- A periodic limb movement disorder index (Total PLMS arousal index) >15 events/hour in PSG
- Significant sleep apnea and loss of REM atonia in PSG
- Recent or recurrent history of musculoskeletal injury or surgery
- Melatonin intake in the last two weeks

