5. Polysomnography (PSG) is an established sleep test in PD and will be measured at home at the participants own convenience, before and after 4 weeks of the supplemental light exposure and the following two weeks without supplemental light exposure (to determine the duration of effect of light exposure, “wash out”). It non-invasively records, through sensors attached to i.e. the head, arm, chest and legs, information used to evaluate sleep staging, eye and limb movement. A member of the research team will place the sensors on the participant on completion of the first laboratory visit in order to measure sleep functions during the night before the start of the light intervention. The research staff will visit the participant’s home the next morning to remove the sensors. After four weeks of light intervention, the research staff will return to the participant’s home in the afternoon and places the sensors for the second (post-intervention) polysomnography sleep test. Sensors will be removed the next day on their second laboratory visit. Two week later the researcher will return to the participants home to set up sensors for the final PSG to determine the long-term effects of supplemental light exposure (see 7.7 schedule of measurements in **Table 1** above). Sleep data analysis and training of research team members in analysis will be performed by [name] who is an accredited sleep physician.
6. Established tests for motor assessment will be applied in addition to the MDS-UPDRS. The positive effect of light on motor function is less clear in PD and is thought to be influenced by the changes in melatonin secretion patterns from the pineal gland. Moreover, improved motor function due to “sleep benefit” is attributed to increased dopamine storage during sleep. In addition, our research demonstrated that deep brain stimulation of areas central to sleep (pedunculopontine nucleus) can improve gait. Both gait and balance measures are established methods for determining motor function in PD and with which we have extensive experience.  

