## 6. Statistical plan

### 6.1. Sample size determination and power

Power and Sample size calculation are based on established formulae. Mean difference data (effect size) are based on studies in PD by Breen et al 2014, Dumpala et al 2019, Xu et al 2014, Videnovic et al 2017, Zulai et al 2019, Rehman et al 2019 and Paus & Schmitz-Hubsch 2007. A minimum sample size of 60 persons will be required to statistically detect a minimum meaningful difference as per outcome measures. This assumes a type I error of 5% (two tailed) and a type II error of 10% (90% power). We assume a response rate of 75% and allow 15% extra participants for multivariable statistical modelling to adjust for confounding factors (a 1.89x inflation).

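### Eleven primary outcomes at two visits have no deciding comparison and no multiplicity adjustment, so the 5% type I error is not controlled across the primary family and the 90% power is a per-test figure

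*Combined protocol and SAP*

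**What the plan says.** The supplement (Endpoints, Primary) lists these sleep variables: "Sleep stages (N1, N2, N3, REM), Total sleep time, Sleep onset latency, Stage REM latency, Sleep efficiency, Time awake, Total PLMS Arousal Index". Counting each stage, that is ten. DLMO is added as a further primary outcome, and all eleven are assessed as change at both week 4 and week 6.

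Protocol section 2.2 also makes DLMO and polysomnography primary at both visits, but its sleep list is shorter: "total sleep time, sleep efficiency and latency and REM latency and time in sleep stages". Time awake and the PLMS arousal index are not in it.

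The two visits answer different questions. By section 5.5, item 5, the week 6 recording follows "the following two weeks without supplemental light exposure" and serves to show how long an effect lasts.

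The trial is sized once, in section 6.1: "A minimum sample size of 60 persons will be required to statistically detect a minimum meaningful difference as per outcome measures". The error rates are given in one sentence: "This assumes a type I error of 5% (two tailed) and a type II error of 10% (90% power". No division of the 5% among outcomes or visits is mentioned.

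Section 6.2 and the supplement's Statistical analyses section fit the same mixed model to every outcome (group, categorical time and their interaction) and then examine group and time differences post hoc. Neither names a lead outcome, visit or contrast, a testing order, a rule that all outcomes must succeed, or an adjustment. The only correction named is Bonferroni, for baseline melanopsin function against healthy controls.

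**The concern.** If no rule says which result decides the trial, any one of the listed comparisons can be presented as a positive primary result, including one obtained two weeks after the light stopped. With no real effect, the chance that at least one falls below 0.05 is well above 5%. A reader who takes the 5% and 90% in section 6.1 as properties of the trial's primary conclusion would be misled. The first is not controlled over the family, and the second would not survive controlling it. What the trial may claim is therefore at stake. The validity of any single estimate is not.

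**Working it through.** **Inputs.** Two-sided 5% and 90% power (section 6.1). Ten sleep variables plus DLMO at two visits (supplement). Eight sleep variables plus DLMO at two visits (section 2.2). Correlations between outcomes and visits are not in the documents, so a range is assumed.

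**The plan's own figure.** The 60 cannot be reproduced. Section 6.1 says "Mean difference data (effect size) are based on studies in PD by" and then names studies, without a difference or SD for any outcome. The steps below are chosen so that most need neither.

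**Step 1, the count.** Supplement: (4 stages + 6 others + DLMO) × 2 visits = 11 × 2 = 22. Section 2.2: (4 stages + total sleep time + efficiency + sleep latency + REM latency + DLMO) × 2 = 9 × 2 = 18. One group-by-time test per outcome: 11 or 9.

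**Step 2, family-wise error with each test at 5%.** If independent, 1 − 0.95^m. With common correlation ρ, it is 1 − ∫ φ(x) [Φ((1.96 − √ρ·x)/√(1−ρ)) − Φ((−1.96 − √ρ·x)/√(1−ρ))]^m dx.

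| Family | m | ρ = 0 | 0.3 | 0.5 | 0.7 | 0.9 |
|---|---|---|---|---|---|---|
| Supplement list, both visits | 22 | 68% | 57% | 44% | 30% | 16% |
| Section 2.2 list, both visits | 18 | 60% | 51% | 40% | 28% | 15% |
| Supplement list, one test each | 11 | 43% | 37% | 30% | 22% | 13% |
| Section 2.2 list, one test each | 9 | 37% | 33% | 27% | 20% | 12% |

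A simulation with separate correlations between outcomes (0.3 to 0.9) and between visits (0.5 to 0.8) gives 58% down to 20% for 22 tests. Only perfect correlation returns 5%.

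**Step 3, power per test once the family is controlled.** A test with 90% power at 5% has a standardised effect of 1.960 + 1.282 = 3.242. At a Bonferroni level 0.05/m its power is Φ(3.242 − z), with z the two-sided critical value.

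- m = 22: level 0.00227, z = 3.052, power Φ(0.189) = 57.5%.
- m = 18: level 0.00278, z = 2.991, power 59.9%.
- m = 11: level 0.00455, z = 2.838, power 65.7%.

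A t-based version for 22 tests, assuming 30 analysed per arm and 1:1 allocation, gives 54% (effect 0.85 SD). If the 60 already contains the 1.89-fold inflation of section 6.1, then 60/1.89 = 31.7, about 16 per arm, and the figure is 52% (effect 1.18 SD). Keeping 90% per test over 22 would need ((3.052 + 1.282)/3.242)² = 1.79 times the sample, about 108.

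Max-T control, which uses the correlation between tests, gives 58% to 74% per test (between-outcome correlation 0 to 0.9, between-visit 0.5 to 0.8).

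**Step 4, other decision rules.** If all 22 had to succeed, the 5% would be protected, but joint power would be 0.9^22 = 9.8% if independent and at most 72% in the correlations simulated. If any one could succeed after Bonferroni, power would be 84% to 100%, provided every outcome has the planned effect. The plan states neither rule.

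**The case against.** Five points can be made for the plan.

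- **The 5% may be per test.** A reader might infer that 5% and 90% contradict each other. They do not: section 6.1 never calls the 5% family-wise and refers to outcome measures in the plural. Read one test at a time, the two are compatible. This stands. What remains is that the plan does not say so and offers nothing at the level of the family.
- **The count is not fixed.** A reader might take 22 as a minimum. It is the supplement's count. Section 2.2 gives 18, and the interaction model, with the single group-by-time p value per outcome shown in Table S1, would give 9 to 11. If every p value in that layout counted, there would be more than 22. This stands too, but family-wise error exceeds 5% on every one of these readings.
- **The variables are dependent.** Stages, total sleep time, efficiency and time awake overlap, so 68% is an upper figure and plain Bonferroni is conservative. Ranges are therefore given.
- **The side issues are not errors.** Week 6 is primary in both lists and has a stated purpose. The section 2.2 list opens with *i.e.*, which this protocol elsewhere uses for examples, so the mismatch with the supplement needs clarifying but need not be a change of endpoint. A reader might also argue that the exclusion criterion "A periodic limb movement disorder index (Total PLMS arousal index) >15 events/hour in PSG" truncates a primary outcome. It restricts entry in both arms alike, does not cap later values, and does not inflate type I error.
- **This is a proof-of-concept trial** (section 1.2) with comparisons described as exploratory. That argues for modest claims. It does not supply a decision rule for endpoints labelled primary.

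Table S1 does suggest some adjustment of time contrasts within an outcome: for BDI-II, week 4 minus baseline has an interval of −2.81 to −0.19 but p = 0.07, close to a Tukey value of 0.065 and unlike the unadjusted 0.025. The group contrasts checked there match unadjusted p values, so this does not cover the primary between-arm family.

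**Conclusion.** The point holds as an omission. The plan has many primary comparisons and no rule for deciding among them. The 5% is uncontrolled across the primary family: about 68% down to 16% for 22 tests and 37% down to 12% for 9, at assumed common correlations of 0 to 0.9. Control would bring a 90% test to about 54–58% with Bonferroni over 22 (52% if only 16 per arm are analysed), 66% over 11, and about 58–74% with a correlation-based method. The stated 90% is thus a per-test figure only, and even that cannot be checked without a difference and SD.

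The correlations, the 1:1 allocation and the numbers analysed per arm are assumptions. The 57.5%, 60% and 66% normal-approximation figures need none of these.

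The documents do not support saying that the stated error and power are mutually impossible, that 22 is a floor, or that placing week 6 among the primaries is itself a mistake.

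**What to change.** 1. Define the primary contrast for every outcome as the between-arm difference in change from baseline.
2. Keep every pre-specified primary outcome and visit, and report Holm or max-T adjusted p values over the whole primary family at 5% overall, beside the unadjusted estimates and confidence intervals. Claim primary success only on adjusted results.
3. Reword section 6.1 so that 5% and 90% are labelled per test, and add the power under the family-wise procedure.
4. Reconcile the primary lists in section 2.2 and the supplement, stating whether time awake and the PLMS arousal index belong.

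Narrowing to DLMO and one sleep variable at week 4, tested with Holm, would be simpler. At the stricter Holm level of 0.025 the power per endpoint is Φ(3.242 − 2.241) = 84%. The file already reports results (Figures S1 and S2, Tables S1 and S2), so this is valid only if the choice was made before unblinded data were seen. Otherwise it must be labelled post hoc. The documents give no basis for preferring one sleep variable over another.

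The cost is a change of wording and one extra column of p values. Fewer results can be called significant, and the stated power per outcome becomes less favourable.

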### Key secondary

- Change from baseline to week 4 and week 6 in mean: PSQI total score, PSQI bed partner reported sleep quality, PDSS and ESS total score

### Other Secondary (motor)

- Change from baseline to week 4 and week 6 in mean: stride velocity, total double support, balance (average velocity of centre of pressure) and dominant frequency both hands for resting and postural tremor

### Exploratory:

- Change from baseline to week 4 and week 6 in mean PDQ-39 total score, BDI-II total score and MDS-UPDRS total and motor scores

During the 6 weeks of the study duration, participants wore an actigraphy wristwatch (GENE Active V3.1, Activinsights Ltd, UK) to record environmental light exposure.

- The daytime light exposure levels were adjusted as per the sunrise and sunset times given by the geodetic calculators provided Geoscience Australia (<https://geodesyapps.ga.gov.au/sunrise>) for Brisbane Australia.
- The weekly average of light exposure were compared between the groups over the six weeks of the study period
- For adherence, the illuminance data were also used to verify the ambient light level during the salivary sample collection

## Schedule of measurements and durations

|                                                                                                                                                                                                                                                                                                                                                                                                                                                                                                                                                                                                                                                                                                                                                                          |
|--------------------------------------------------------------------------------------------------------------------------------------------------------------------------------------------------------------------------------------------------------------------------------------------------------------------------------------------------------------------------------------------------------------------------------------------------------------------------------------------------------------------------------------------------------------------------------------------------------------------------------------------------------------------------------------------------------------------------------------------------------------------------|
| Laboratory visit 1 (baseline) ~ 3 hours with breaks                                                                                                                                                                                                                                                                                                                                                                                                                                                                                                                                                                                                                                                                                                               |
| Screening: Ophthalmic slit lamp and fundus grading (front and back of the eye), dementia screening (ACE) and PD stage/severity assessment (MDS-UPDRS, Hoehn & Yahr)
Randomisation to light intervention
Provide Questionnaires (sleep, mood, quality of life and chronotype):
PSQI, ESS, PDSS, Beck's Depression Inventory-II, PDQ-39, MEQ
Pupillography = measure the pupil diameter to assess melanopsin function
Motor function (gait, balance and tremor)
Polysomnography (PSG) sensors set up (objective sleep test for measuring sleep quality through skin electrodes – i.e. eye movements, brain waves, limb movements)
Provide Salivettes and instructions for baseline sleep hormone collection (Dim Light melatonin, DLMO) and actigraph |
| Pre-intervention at home (same day as 1 st laboratory visit at home)                                                                                                                                                                                                                                                                                                                                                                                                                                                                                                                                                                                                                                                                                   |
| Complete questionnaires (if not done at 1 st laboratory visit)
Baseline DLMO (collection of salivary samples) every hour over 6 hours before bedtime and 1 hour after going to bed
Sleep test (Polysomnography, PSG) overnight                                                                                                                                                                                                                                                                                                                                                                                                                                                                                                                          |
| Research staff visit at home (next morning after laboratory visit 1) ~1 hour                                                                                                                                                                                                                                                                                                                                                                                                                                                                                                                                                                                                                                                                                      |
| Collect pre-intervention DLMO baseline and completed questionnaires
Provide and instruct in the use of the light box (timed as per MEQ chronotype determination)
PD stage/severity assessment (MDS-UPDRS, Hoehn & Yahr (if not done at first laboratory visit)                                                                                                                                                                                                                                                                                                                                                                                                                                                                                                     |
| Intervention at home                                                                                                                                                                                                                                                                                                                                                                                                                                                                                                                                                                                                                                                                                                                                              |
| As per randomisation: Light intervention for 30 min per day over 4 weeks (at a time determined with MEQ chronotype)
Actigraphy over 4 weeks (to measure light exposure)
Sleep diary over 4 weeks (~5 min per day)
At week 2, research staff visit at home to exchange actigraphs for data download & recharge and to provide a new actigraph for the following 2 weeks (~15 min visit)                                                                                                                                                                                                                                                                                                                                                                   |
| Research staff visit at home (afternoon/night before 2 nd laboratory visit) (~30 min -1 hour)                                                                                                                                                                                                                                                                                                                                                                                                                                                                                                                                                                                                                                                          |
| Provide Salivettes for post-intervention DLMO and questionnaires at week 4
Polysomnography (PSG) sensor set up for overnight sleep test at week 4                                                                                                                                                                                                                                                                                                                                                                                                                                                                                                                                                                                                                     |
| Laboratory visit 2 (week 4) (~2-3 hours with breaks)                                                                                                                                                                                                                                                                                                                                                                                                                                                                                                                                                                                                                                                                                                              |
| Collect post-intervention DLMO week 4
Collect Questionnaires (sleep, mood, quality of life):
PSQI, ESS, PDSS, Beck's Depression Inventory-II, PDQ-39, MDS-UPDRS
Pupillography (melanopsin function)
Motor function (gait, balance and tremor)                                                                                                                                                                                                                                                                                                                                                                                                                                                                                                                |
| Post-intervention at home (2 weeks)                                                                                                                                                                                                                                                                                                                                                                                                                                                                                                                                                                                                                                                                                                                               |
| Actigraphy over 2 weeks (wrist worn watch)
Sleep diary over 2 weeks (5 min per day)                                                                                                                                                                                                                                                                                                                                                                                                                                                                                                                                                                                                                                                                                   |
| Research staff visit at home (afternoon/ night before 3 rd laboratory visit) (~30 min -1 hour)                                                                                                                                                                                                                                                                                                                                                                                                                                                                                                                                                                                                                                                         |
| Provide Salivettes for post-intervention DLMO and questionnaires at week 6
Set up polysomnography sensors for overnight sleep test at week 6                                                                                                                                                                                                                                                                                                                                                                                                                                                                                                                                                                                                                          |
| Laboratory visit 3 (week 6) (~2-3 hours with breaks)                                                                                                                                                                                                                                                                                                                                                                                                                                                                                                                                                                                                                                                                                                              |
| Collect post-intervention DLMO week 6
Collect Questionnaires (sleep, mood, quality of life):
PSQI, ESS, PDSS, Beck's Depression Inventory-II, PDQ-39, MDS-UPDRS
Pupillography
Motor function (gait, balance and tremor)                                                                                                                                                                                                                                                                                                                                                                                                                                                                                                                                      |

